### Intervention adherence monitoring

Adherence to the weight management intervention is monitored using a combination of objective measurements via number of diet products sent to the participant over time, via dietetic consultations, and via engagement with the digital resources made available. These quantitative data will be used in the process evaluation to describe factors such as fidelity to the intervention, dose (based on interactions with the programme) and reach and to examine mediators and moderators of effects.

### Safety reporting

Adverse events (AEs) will not be reported during the course of the trial. Counterweight dietitians will be asked to collate and report only serious adverse events (SAEs) to the study researchers, who will log them into the eCRF and escalate to sponsor pharmacovigilance where related and unexpected.

There is little risk to participants taking part in this study; however, there may be side effects (expected events) from rapid weight loss, relating to the induction period using the total diet replacement sachets (shakes and soups) such as constipation, increased sensitivity to cold, headache, and dizziness (which were commonly reported side effects in the DiRECT study and dissipated over time). Other side effects that are less commonly reported are: fatigue, mood changes, nausea, diarrhoea, indigestion, hair loss. All participants are provided with information on all possible side effects and management strategies should they be problematic. These events would be considered expected within this study.

We do not plan provisions for ancillary or post-trial care. The sponsor (NHS Greater Glasgow and Clyde) will be liable for negligent harm caused by the design of the study. NHS indemnity is provided under the Clinical Negligence and Other Risks Indemnity Scheme (CNORIS).

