### Study design

This registered randomised controlled trial (ISRCTN12595520, protocol registered 25/11/2021) uses a wait-list controlled design, with participants allocated at baseline in a 1:1 ratio to one of two groups using a mixed approach of minimisation (80%) and randomisation (20%). The treatment allocation is performed by a registered Clinical Trials Unit and is designed to maintain balance with respect to the dominant Long COVID symptom (fatigue, breathlessness, pain, anxiety/depression, other), sex (male, female, or other), age (<50, ≥50), self-reported ethnicity using UK Census classifications (White, South Asian, Other) and postcode-based index of multiple deprivation (IMD)) (<median, ≥median).

Participants are randomised to one of two study groups:

Treatment: evidence-based weight management programme (Counterweight-Plus, delivered and supported by Counterweight Ltd)Control: standard care (delayed entry to the Counterweight-Plus programme after six months)

The weight management programme includes a formula low-energy diet for eight to 12 weeks to induce weight loss, food reintroduction and weight loss maintenance (week 8/12 to month six). The impact of the intervention on the patient’s dominant symptom will be assessed at the six-month mark. After six months, observation will continue up to 12 months for cross-sectional analysis of long-term maintenance of weight loss. Participants in the control group will be offered delayed entry to Counterweight-Plus programme at this point and will add observational data to the 12-month time point, but not form part of the RCT analysis (
Figure 1).

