**Figure 1. f1:**
[figure not shown]
ReDIRECT trial flow diagram. The ReDIRECT Study is a parallel, non-blinded, wait-list controlled study with 240 participants allocated in a 1:1 ratio either to the Counterweight-Plus weight management programme (treatment) or to continue usual care (control group with delayed entry to the Counterweight-Plus programme after 6 months). The effectiveness of the trial will be evaluated after six months. Further data will be collected after six months to the end of the trial for additional observational analyses. Blue: treatment group (immediate entry to Counterweight); Orange: control group (usual care); CWT: Counterweight; RCT: randomised controlled trial.

The study is open-label due to the nature of the intervention and participants, researchers (who enrol the participants and organise all follow-ups), and dietitians (who deliver the intervention) are aware of the treatment allocation. However, the study statistician will remain blinded to the allocation until completion of the statistical analysis plan and locking of the database up to six months post-randomisation.

There are no pre-specified criteria for discontinuing the intervention or modifying the allocation. The intervention may be discontinued as per a participant’s wishes, or as a result of adverse events making pursuing the intervention incompatible with care. In the event of a participant discontinuing the intervention, participant follow-up remains in place to collect outcome data.

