### Study outcome measures

Outcomes are all measured for both groups at baseline, three, and six months. Follow-ups for cross-sectional analysis are measured at 12 months in the treatment group and nine, 12, and 18 months for the control group, with the exception of height, which is recorded at baseline only.

Due to geographical constraints for this UK-wide trial coupled with COVID-19 constraints, all trial outcomes are self-reported, using a bespoke electronic case report form (eCRF). Remote measurement is anticipated to minimise participant burden and cost and to maximise retention. To facilitate self-reported measurements of weight and blood pressure, participants receive digital scales (Model UC-502, A&D Instruments Ltd, Abingdon, UK) and fully automatic blood pressure monitors (arm type monitor TMB-1970, Kinetik Medical Devices Ltd, Redhill, UK) by post. Other measurements are collected through the eCRF / web-based questionnaires, with all entries verified by the study researchers, who are available to liaise and assist participants throughout the study.

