### Statistical analysis

At the design stage for the trial, the primary outcome was proposed as the self-selected, most troublesome symptom (fatigue, breathlessness, pain, anxiety/depression, or another symptom as selected by the participant). Since each outcome measure will have a different distribution, the proposal was to standardise each measure by subtracting the mean and dividing by the standard deviation (SD) from those participants who selected that symptom as their most troublesome. The suitability of this measure for the primary analysis will be assessed during the trial, as data accrue, in blinded analyses. Reports to the Trial Steering Committee (TSC) include assessments of the distribution of this measure, and the committee will advise and approve the final choice of primary outcome and its analysis. The TSC will approve the final Statistical Analysis Plan, prior to locking the six-months dataset and unblinding the statistical team.

The proposed analysis of the primary outcome at six months will be to compare randomised groups using a linear regression model, adjusting for the baseline value of the primary outcome, and factors used to balance the randomisation/minimisation procedure. We do not plan interim analyses. The intervention effect will be reported as the adjusted mean difference between groups, with a 95% confidence interval, and p-value. The analysis will be according to the intention-to-treat principle, in that participants will be analysed according to their randomised group, regardless of compliance with the intervention.

Secondary analyses will use linear or logistic regression, as appropriate, to estimate between-group differences or odds ratios for secondary outcomes. Missing data will not be imputed initially, but the sensitivity of main analyses will be explored using multiple imputation, and analyses weighted by the inverse probability of follow-up, based on a non-parsimonious model of the probability of being followed up, as a function of baseline characteristics. Associations between baseline characteristics, primary and secondary outcomes will be explored by extending the main analysis regression models.

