### Sample size

Assuming the SD of the primary outcome at follow-up (derived from the symptom score at follow-up, standardised using the same mean and SD as used at baseline) is one, then to have 90% power to detect a between group difference of 0.5 at follow-up, at a 5% significance level, requires a sample size of 86 per group with follow-up data. To allow for attrition, we aim to randomise 240 people.

If the intervention proves to be acceptable and safe, the 120 participants originally allocated to the control group will be offered the intervention as a delayed entry group. Their results (some may exceed the lifetime of the project) will be analysed as observational data and used to increase the study power for hypothesis generation, e.g., to explore relationships between extent of weight change and Long COVID symptoms.

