### Trial management

The study is coordinated by the Study Management Group (SMG), consisting of all co-applicants, the project manager and representatives from both NHSGGC and other organisations relevant to the study. The role of the group is to monitor all aspects of the conduct and progress of the study, ensure that the protocol is adhered to and take appropriate action to safeguard participants and the quality of the trial itself. The SMG meets on a bi-monthly to monthly basis.

A Trial Steering Committee (TSC) provides overall supervision of the trial and ensures that it is being conducted in accordance with the principles of good clinical practice (GCP) and the relevant regulations. It includes an independent chairperson, an independent statistician and clinical trials specialist, an independent health economist, the sponsor and an independent patient representative. The TSC meets every four months and reviews the trial protocol, agrees substantial protocol amendments, and provides advice to the investigators on all aspects of the trial. Decisions about continuation or termination of the trial or substantial amendments to the protocol are the responsibility of the TSC who will advise the sponsor.

As this study is not classed as a Clinical Trial of an Investigational Medicinal Product (CTIMP), there is no Data Monitoring Committee (DMC) for ReDIRECT.

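### The only serious adverse event route described runs through the intervention dietitians, with none named for controls during the six randomised months, so SAE counts by arm would be biased towards apparent harm.

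*Protocol article*

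**What the plan says.** **Collection of events.** The Safety reporting section of the protocol article first rules out non-serious events: "Adverse events (AEs) will not be reported during the course of the trial". It then gives one chain for serious events: "Counterweight dietitians will be asked to collate and report only serious adverse events (SAEs) to the study researchers". The researchers log these in the eCRF and escalate those that are related and unexpected. No other starting point for an SAE report is named.

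**Who sees whom.** The Study design section describes the comparator as "Control: standard care (delayed entry to the Counterweight-Plus programme after six months". The text under Figure 1 notes that "researchers (who enrol the participants and organise all follow-ups), and dietitians (who deliver the intervention) are aware of the treatment allocation". Study outcome measures adds: "Outcomes are all measured for both groups at baseline, three, and six months". Table 2 includes healthcare utilisation, medication and blood pressure as well as the symptom scales.

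**Control entry.** The Sample size section attaches a proviso: "If the intervention proves to be acceptable and safe, the 120 participants originally allocated to the control group will be offered the intervention". The abstract and Study design describe delayed entry without it. Statistical analysis states "We do not plan interim analyses", and Trial management states "there is no Data Monitoring Committee (DMC) for ReDIRECT". Trial management also sets up a Trial Steering Committee (TSC) with an independent chair and an independent statistician. It meets every four months and is responsible for decisions on continuing or stopping the trial.

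**The concern.** A between-arm count of serious events can be read only if an event has a similar chance of being recorded in either arm. Here the people who start the report are those who deliver the programme. Intervention participants have regular dietitian appointments and messages; controls have none of this contact until month six. Followed as written, the procedure records events in one arm and has no stated means of recording them in the other.

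The error has a known direction: it makes the intervention look worse. Leaving out non-serious events removes the other direct source. Several of the expected effects listed under Safety reporting, such as constipation, dizziness and hair loss, have no instrument in Table 2 unless a participant's free-choice symptom happens to cover them.

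What is at stake is any statement about SAEs by arm in the final report. The primary outcome, its analysis and its power are not affected.

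**Working it through.** **1. The plan's own figure.** The article states no safety figure. Its sample size of 86 per group (difference 0.5, SD 1, 90% power, 5% level taken as two-sided) reproduces: the t-test solution is 85.03, rounded up to 86. It is not in dispute and has no bearing on this point.

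**2. Route by arm, months 0 to 6.**

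| | Intervention | Control |
|---|---|---|
| Contact with dietitians | yes, they deliver the programme | none described |
| Named SAE route | dietitian to researcher to eCRF | none named |
| Non-serious events | not reported | not reported |
| Researcher-run follow-up at 3 and 6 months | yes | yes |

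The second row differs by arm. The fourth does not, and it is where a common procedure could sit.

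**3. Size of the bias.** Input from the article: 120 per arm. Assumptions, none of them in the article: the same true six-month SAE risk *p* in both arms (2%, 5% or 10%), 90% capture in the intervention arm, and control capture *s* from 0% to 90%. Recorded counts are X ~ Binomial(120, 0.9*p*) in the intervention arm and Y ~ Binomial(120, *s·p*) in controls. A spurious excess means X > Y with two-sided Fisher exact p < 0.05.

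With *s* = 0, Y is always 0. Fisher gives p = 0.060 for 5 v 0 and p = 0.029 for 6 v 0, so a spurious excess needs X ≥ 6:

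- *p* = 2%: expected X = 120 × 0.018 = 2.2; P(X ≥ 6) = 0.022
- *p* = 5%: expected X = 120 × 0.045 = 5.4; P(X ≥ 6) = 0.455
- *p* = 10%: expected X = 120 × 0.09 = 10.8; P(X ≥ 6) = 0.964

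The range over control capture, with apparent risk ratio 0.9/*s*:

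| Control capture | Apparent risk ratio | *p* = 2% | *p* = 5% | *p* = 10% |
|---|---|---|---|---|
| 0% | undefined (no control events) | 2% | 46% | 96% |
| 25% | 3.6 | 1% | 17% | 47% |
| 50% | 1.8 | 1% | 6% | 15% |
| 90% (equal) | 1.0 | 0.3% | 1.0% | 1.4% |

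The apparent ratio is wrong in every row but the last, whether or not a test would reach significance.

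**4. What one arm can show alone.** With 0 SAEs in 120 intervention participants, the one-sided 95% upper bound on risk is 1 − 0.05^(1/120) = 2.5%. A judgement on the intervention arm by itself is therefore possible, provided its own capture is good.

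**5. Timing of control entry.** Recruitment ran from December 2021 to July 2022. The first controls reach six months about June 2022 (December 2021 + 6 months). The last six-month data arrive about January 2023 (July 2022 + 6 months). For about seven months, controls could enter before the randomised comparison is complete. The Sample size section gives no criterion, data source or decision point for its proviso.

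**The case against.** The strongest reply is that the article does not make the dietitians the sole reporters. In the quoted sentence, the word only limits the type of event, not who reports it. The researchers who log SAEs also organise follow-up in both arms, check all entries and liaise with participants, and nothing bars them from logging a control event. This stands. A reader might infer that control SAEs cannot be recorded; the article shows only that no route for them is named. A fuller protocol may give one. Still, the chain that is described starts with staff attached to one arm, and chance reports from controls would not make capture equal.

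Two further inferences go too far:

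- *The arms cannot be compared on safety at all.* Healthcare use, medication, blood pressure and the symptom scales are collected alike in both arms at three and six months. Fatigue and mood, both listed as expected effects, are scored in everyone. A limited indirect comparison is available.
- *The condition that the programme prove acceptable and safe cannot be assessed.* It could be judged from intervention-arm SAEs and the process evaluation, under the TSC. The absence of a DMC and of interim analyses does not rule out such a review. What is missing is a stated criterion, source and date.

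It is also true that the article plans no between-arm test of SAEs. The Fisher calculation measures the distortion in a table by arm; it does not describe a planned analysis. A single scenario such as 6 v 0 proves little by itself, which is why the range is shown.

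**Conclusion.** The point holds in this form. The article states one SAE route, attached to the intervention arm, and names none for controls over the randomised period; non-serious events are reported in neither arm. SAE capture is therefore unequal by arm, and a count by arm would be biased towards apparent harm from the intervention.

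The size is not known from the documents. Under the assumptions above, the chance of a spurious significant excess runs from about 2% to 96% with no control capture, and from about 1% to 15% if half of control events are captured. The direction is firm as long as capture is lower in controls; the magnitude rests wholly on the assumed risks and capture rates.

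The conflict between the abstract, Study design and Sample size sections over conditional entry is real but minor, since control data after month six are observational.

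**What to change.** 1. State one SAE procedure for both arms: the same questions, asked by the researchers at the existing eCRF follow-ups.
2. Recover earlier events in the same way in both arms from the healthcare-utilisation questionnaire and, where participants gave the optional consent, from records linkage.
3. Tabulate SAEs by randomised arm and by source of report, so that dietitian-only reports can be told apart from those found by the common procedure.
4. If this cannot be done, say in the report that SAE counts are not comparable between arms.
5. Reconcile the abstract, Study design and Sample size sections on whether control entry is conditional. If the condition is kept, give its criterion, data source and decision point.

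**Cost.** A few questionnaire items, one table and some text; no new visits. Questionnaires become slightly longer for participants with fatigue. Recruitment closed in July 2022, so the last three-month follow-ups fell about October 2022 and the last six-month ones about January 2023. Much of the randomised period would therefore be covered only by recall or by data already collected.

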### Data management

An electronic case report form (eCRF), developed by the Robertson Centre for Biostatistics, captures all data required to meet this protocol’s requirements. Access to the eCRF is restricted, via a trial-specific web portal, and only authorised personnel will be able to make entries or amendments to the participants’ data via the web portal. It is the investigator's responsibility to ensure completion and confirm that the data is accurate, complete and verifiable. Data will be stored in a MS SQL Server database.

Where it is practical, data will be validated at the point of entry into the eCRF. Any additional data discrepancies will be flagged to the investigator and any data changes will be recorded in order to maintain a complete audit trail (reason for change, date change made, who made the change).

The Robertson Centre for Biostatistics systems are fully validated in accordance with industry and regulatory standards and incorporate controlled access security. High volume servers are firewall protected and preventative system maintenance policies are in place to ensure no loss of service or data. Web servers are secured by digital certificates. Data integrity is assured by strictly controlled procedures, including secure data transfer procedures. Data are backed up on-site nightly and off-site to a commercial data vault weekly. The Robertson Centre for Biostatistics has an ISO 9001:2008 quality management system and ISO 27001:2013 for Information Security and is regularly inspected against the standards by the British Standards Institution.

Personal information will be collected via the eCRF to enable participant completion of questionnaires and to facilitate intervention delivery and record linkage. These data items will be encrypted and only those individuals who require to see these data, i.e., research staff, dietitians or the person performing record linkage, will be able to view them. All electronic data will be held securely in accordance with ISO 27001:2013 at the Robertson Centre for Biostatistics, part of the Glasgow Clinical Trials Unit. All Centre staff are required to sign confidentiality agreements and to follow Standard Operating Procedures in accordance with Good Clinical Practice and ISO certification.

The trial data managers, statisticians, health economists or any other staff who will perform data related tasks will only be able to access depersonalised data where the participant’s identifying information is replaced by a unique study identifier. Only those that have been trained and approved will be able to enter or view any data via the web portal.

Participant consent forms will be stored in a secure password-protected folder on the University of Glasgow servers.

Study investigators based at the University of Glasgow and NHS Greater Glasgow and Clyde will have access to the final dataset. This will be restricted to the relevant staff involved in drafting and reviewing the final study report. The final dataset will be backed-up on a secure university folder, with password protection.

### Statistical analysis

At the design stage for the trial, the primary outcome was proposed as the self-selected, most troublesome symptom (fatigue, breathlessness, pain, anxiety/depression, or another symptom as selected by the participant). Since each outcome measure will have a different distribution, the proposal was to standardise each measure by subtracting the mean and dividing by the standard deviation (SD) from those participants who selected that symptom as their most troublesome. The suitability of this measure for the primary analysis will be assessed during the trial, as data accrue, in blinded analyses. Reports to the Trial Steering Committee (TSC) include assessments of the distribution of this measure, and the committee will advise and approve the final choice of primary outcome and its analysis. The TSC will approve the final Statistical Analysis Plan, prior to locking the six-months dataset and unblinding the statistical team.

The proposed analysis of the primary outcome at six months will be to compare randomised groups using a linear regression model, adjusting for the baseline value of the primary outcome, and factors used to balance the randomisation/minimisation procedure. We do not plan interim analyses. The intervention effect will be reported as the adjusted mean difference between groups, with a 95% confidence interval, and p-value. The analysis will be according to the intention-to-treat principle, in that participants will be analysed according to their randomised group, regardless of compliance with the intervention.

Secondary analyses will use linear or logistic regression, as appropriate, to estimate between-group differences or odds ratios for secondary outcomes. Missing data will not be imputed initially, but the sensitivity of main analyses will be explored using multiple imputation, and analyses weighted by the inverse probability of follow-up, based on a non-parsimonious model of the probability of being followed up, as a function of baseline characteristics. Associations between baseline characteristics, primary and secondary outcomes will be explored by extending the main analysis regression models.

Subgroup analyses will be carried out by including the subgroup variable and its interaction with treatment group in these models. Prespecified subgroups of interest will include sex, age, ethnicity, socioeconomic status (based on postcode index of multiple deprivation), main symptom, and baseline BMI. We will also consider analysis by recruitment source (social media vs primary care) if possible. Additional exploratory analyses will investigate if short-term differences between randomised groups (particularly early weight loss) are predictive of six-month intervention effects. Additional observational analyses will explore within-group changes in outcomes between six and 12 months in both randomised groups, and predictors of long-term outcomes in the intervention arm of the trial. 

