### Weight loss induction phase (from week 0 to week 8–12)

Counterweight provides 8–12 weeks of a low-energy, nutritionally complete, formula diet (850 kcal/day) to replace all meals (total diet replacement, TDR), aiming for ≥15 kg (or 15% of their body weight if over 100kg) weight loss. Products include a variety of soups and shakes provided free of cost to the participant. Those who are unable, or prefer not to, follow the TDR formula diet (10% in the published DiRECT study (
Lean *et al.*, 2018)) are offered an alternative approach providing 1200 kcal/day, either a meal replacement diet in which a maximum of two meal replacements are consumed per day or a food-based low-carb or low-fat approach. Food used to supplement the TDR or for fully food-based plans is purchased by the participants and not provided by the study. To increase adherence to the programme, support is tailored to individual participants, allowing for flexibility around commitments or life events. Further strategies are pre-emptively discussed, e.g., the possibility of adding in one meal/day or including ‘days off’, with encouragement to resume the full TDR at subsequent visits and to maintain whatever weight has already been lost and moving onto the maintenance phase early if necessary to avoid dropping out altogether.

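### The two named missing-data sensitivity analyses do not, as described, relax missing at random; a delta-adjusted version with shifts varied by arm is a cheap addition

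*Protocol article*

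**What the plan says.** Under Statistical analysis, the protocol article sets out a main analysis without imputation: a linear regression of the six-month primary outcome on randomised group, its baseline value and the balancing factors. For missing data, "the sensitivity of main analyses will be explored using multiple imputation, and analyses weighted by the inverse probability of follow-up". The follow-up model behind the weights is to be large, but is built from baseline characteristics. Nothing is said about the imputation model. No delta-adjusted, reference-based or tipping-point analysis is named. The same section says that the Trial Steering Committee will approve the final statistical analysis plan before the six-month data are locked and the statistical team is unblinded.

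These design features bear on the point:

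- Study design: the trial is open-label, and controls are offered "delayed entry to the Counterweight-Plus programme after six months". Participants who stop the intervention remain in follow-up for outcome data.
- Study outcome measures: all outcomes are self-reported and are collected at baseline, three and six months in both arms.
- Weight loss induction phase: the flexible options include "moving onto the maintenance phase early if necessary to avoid dropping out altogether".
- Sample size: the calculation "requires a sample size of 86 per group with follow-up data", and then "To allow for attrition, we aim to randomise 240 people".

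**The concern.** A sensitivity analysis tests an assumption only if it departs from it. The complete-case regression is valid if, given arm and the adjustment variables, loss is unrelated to the unseen six-month score. Weighting on baseline variables makes essentially the same assumption with a wider set of baseline predictors. Standard multiple imputation does too, perhaps with three-month data added.

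The design gives reasons to doubt that assumption, and to doubt it differently in the two arms. Controls have the programme ahead of them at month six, which may keep them responding. Intervention participants whose symptoms have not improved know their allocation and may be less inclined to complete remote questionnaires.

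If intervention participants with worse scores were lost more often, the complete-case and weighted estimates would move towards benefit together, and the imputed estimate would move part or all of the way with them. A report could then describe the result as robust to missing data when the relevant possibility had not been examined.

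**Working it through.** **Inputs from the Sample size section.** The calculation is "to have 90% power to detect a between group difference of 0.5 at follow-up", "at a 5% significance level" (two-sided assumed), with a follow-up SD that, "standardised using the same mean and SD as used at baseline) is one".

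**Step 1. Reproduce the plan's figure.** n per group = 2(1.960 + 1.282)² / 0.5² = 2 × 10.51 / 0.25 = 84.1, so 85 by the normal formula. The t-based solution is 85.03, which rounds up to 86. The stated 86 is reproduced.

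**Step 2. Loss the design has room for.** 2 × 86 = 172 and 240 − 172 = 68. Then 68/240 = 28.3%. This is the most that can be lost while keeping 86 per group. It is not a stated forecast.

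**Step 3. Do the named analyses detect outcome-dependent loss?** Two simulations with no true effect and 240 participants were run. Dropout slopes, loss rates and correlations are assumptions, because the article gives none.

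*Simulation A:* 500 trials per scenario, baseline-to-outcome correlation 0.5, about 27 to 30% missing, and imputation by arm from baseline only. Each entry is false benefit in SD / rejection rate.

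| Dependence of loss on the six-month score | Complete case | Weighting | Imputation |
|---|---|---|---|
| None | 0.00 / 6% | 0.00 / 6% | 0.00 / 5% |
| Intervention arm, log-odds 0.5 per SD worse | 0.09 / 9% | 0.09 / 10% | 0.09 / 9% |
| Intervention arm, log-odds 1.0 per SD worse | 0.20 / 36% | 0.20 / 38% | 0.20 / 35% |
| Log-odds 0.5 in opposite directions in the two arms | 0.20 / 32% | 0.20 / 33% | 0.20 / 31% |

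*Simulation B:* 1,500 trials per scenario. Control loss is 20% and unrelated to outcome; intervention loss is 36.6% (28.3% overall). Correlations are 0.5 (baseline with three months), 0.5 (baseline with six months) and 0.65 (three with six months). Imputation is by arm from baseline and the three-month score. Entries are rejection rates, with an independent re-run in brackets.

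| Odds of intervention-arm loss per SD worse | Complete case | Weighting | Imputation |
|---|---|---|---|
| ×1.5 | 14% (12%) | 14% (13%) | 10% (8%) |
| ×2 | 26% (29%) | 27% (31%) | 16% (17%) |
| ×3 | 46% (47%) | 49% (51%) | 30% (32%) |

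Complete-case bias in B was 0.11, 0.17 and 0.25 SD. With an odds ratio of 1, all three methods rejected in about 5% of trials.

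Weighting follows the complete-case result in both simulations. Imputation follows it when only baseline is used, and removes part of the problem when the three-month score is added.

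**Step 4. Tipping point.** Let m be the share missing in the intervention arm, D the observed benefit, and δ the amount by which unseen intervention-arm scores are worse than imputed. The shifted estimate is D − mδ. Significance is lost when δ = (D − c)/m, where c is the smallest significant difference.

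- Unadjusted, 86 per group: c = 1.974 × √(2/86) = 0.301. For D = 0.40, δ = (0.40 − 0.301)/0.283 = 0.35 SD. For D = 0.50, δ = 0.199/0.283 = 0.70 SD. Using 1.96 instead of 1.974 gives 0.36 and 0.71.
- Baseline-adjusted, assumed correlation 0.5: c = 0.301 × √(1 − 0.5²) = 0.301 × 0.866 = 0.261. For D = 0.40, δ = 0.139/0.283 = 0.49 SD. For D = 0.50, δ = 0.239/0.283 = 0.84 SD.
- 10% loss per arm (108 observed per arm), unadjusted: c = 1.96 × √(2/108) = 0.267. For D = 0.40, δ = 0.133/0.10 = 1.33 SD. For D = 0.50, δ = 0.233/0.10 = 2.33 SD.

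**The case against.** The strongest reply is about scope. Only the article is at hand, the final analysis plan is still to be approved, and delta shifts and tipping points are often set out there. The article does not describe its imputation model, and a delta-adjusted analysis is itself usually done by multiple imputation, so it would fit the existing wording. This stands against any claim that the trial has no analysis beyond missing at random. A reader might infer that; the article supports only the narrower statement that none is named in it.

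The second reply concerns the dropout mechanism. No section gives loss by arm or links it to outcome. A reader might take the Weight loss induction phase as predicting missing outcomes, but that text concerns leaving the diet programme. Study design keeps people who stop the intervention in follow-up, which reduces the risk. Intervention participants also have dietitian support for 12 months, and researchers help with data entry. The pull on controls is weaker than it looks: Sample size makes delayed entry conditional on the intervention proving acceptable and safe, and nothing ties entry to completing the month-six data. All of this stands. It makes outcome-dependent loss a possibility, not an expectation.

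The third reply is that the size depends on chosen inputs. That is correct. The 0.40 SD effect is a choice, the design difference of 0.50 doubles the unadjusted tipping shift, and baseline adjustment raises it. At a log-odds of 0.5 in one arm, rejection is only 9 to 10%. Imputation with three-month scores would also depart visibly from the complete-case result, so the three analyses need not agree.

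What the replies leave standing is that the article does fix a strategy: complete cases, baseline-only weights, and imputation with no stated departure from missing at random.

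**Conclusion.** The point holds in limited form. As described, neither named sensitivity analysis relaxes the missing-at-random assumption of the complete-case main analysis, so agreement among them would not establish robustness to outcome-dependent loss. For weighting this follows from the stated baseline-only model; for imputation it is the default reading of an undescribed method.

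At the largest loss the sample size has room for, 28.3%, an observed 0.40 SD benefit could be overturned by a shift of about 0.35 SD (unadjusted) to 0.49 SD (baseline-adjusted). An observed 0.50 SD needs about 0.7 SD unadjusted. At about 10% loss the required shifts exceed 1 SD, and the matter is minor. These figures assume a two-sided test, SD 1 and a baseline correlation of 0.5 where adjusted; the simulated error rates also rest on illustrative dropout slopes.

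The documents do not support a reading that the result will be biased, or that differential dropout is expected. This is a cheap improvement to a stated strategy, not an error in it.

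**What to change.** In the Statistical analysis section, or in the final analysis plan before unblinding, state that the multiple-imputation sensitivity analysis of the primary outcome includes a delta-adjusted version. Shifts should be varied separately by arm, for example from 0 to 1 SD worse in the intervention arm, with and without the same shift in controls. Report the shift at which the conclusion changes, so that readers can judge whether it is plausible given the loss actually seen in each arm. Control-based imputation for intervention participants lost to follow-up is an optional addition.

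The cost is one paragraph and a little programming, with no new data. Because the Trial Steering Committee approves the plan before the database is locked, the change can be prespecified blind. The downside is that the primary result may look less robust.
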